### Primary feasibility outcomes

The time points at which these measurements and secondary feasibility outcomes are taken are presented in the schedule of events table (
Table 5).

**Table 5. T5:** Schedule of events table.

	TIMEPOINTS					
PROCEDURES	T0 0 weeks	T1 2 weeks	T2 4–5 weeks	T3 6 weeks	T4 12 weeks	T5 12–14 weeks
Screening	x					
Consent	x					
Demographics and EDI data	x					
Randomisation	x					
**Intervention**						
Appointment 1		x				
Appointment 2				x		
**Assessment**						
*Primary outcomes:*						
-Recruitment	x					
-Adherence				x		
-Retention					x	
*Secondary outcomes*						
Stroke Knowledge	x				x	
HCCQ	x				x	
PROMIS10		x			x	
PEI SA01					x	
Qualitative interviews						x
**Other variables being measured**						
mRS routinely collected	x				x	
Cognition screen	x				x	
Training material feedback				x		
Mood measures						
PHQ2	x					
PHQ9					x	
GAD7					x	
Economic info						
Health and social care usage		x		x	x	
Work status	x				x	
Admin, programme delivery time	x	x	x	x	x	x
Qualitative interview						x

Table 5 key: HCCQ-Healthcare Climate Questionnaire, PROMIS-10-Patient-reported outcome measurement information system, PEI-Patient enablement instrument, SA01- Substantial amendment 1, mRS-modified Rankin scale, PHQ2-Patient health questionnaire 2, PHQ9-Patient health questionnaire 9, GAD7-Generalised anxiety disorder

1. Recruitment rate (Time point 0 = T0): Proportion of participants randomised relative to the total number meeting the inclusion criteria. Reasons for declining participation will be recorded. The ability to gather baseline and EDI data will be noted as will acceptability of randomisation.

2. Treatment adherence rate (Time point 3 = T3): Proportion of participants in the intervention group who attend both follow-up appointments. When people drop out reasons for this will be obtained.

3. Participant retention rate (T4) - Proportion of all participants that complete the follow-up questionnaires.

### Secondary feasibility outcomes

1. To complete patient reported outcome measures and review their acceptability, accessibility, and responsiveness to inform the primary outcome for a main trial.

i.PROMIS10 - Patient-reported outcome measurement information system. This quality-of-life measure was chosen because it has been found to be more sensitive in people who have mild strokes
^
40,
41
^ (T1 and T4). ii.HCCQ - Health Care Climate Questionnaire Short Form – This is a measure of self-determination, particularly autonomy support in health care appointments
^
42
^ (T0 and T4).iii.PHQ9 – Patient Health Questionnaire – measure of depression
^
41,
43
^ (T4).iv.GAD7 – Generalised Anxiety Disorder – measure of anxiety
^
44
^ (T4).v.PEI - Patient Enablement Instrument – measures whether an appointment with a healthcare practitioner impacts a person’s ability to manage their illness
^
45
^ (T4).

2. To assess stroke knowledge, questions used relate to information that should be provided to patients in their personal stroke record available at:
https://www.stroke.org.uk/sites/default/files/professionals/jn_2223-055_-_personal_stroke_record.pdf This document (patient passport) was developed by the Stroke Association in collaboration with stroke survivors, their families, clinicians, and NHS England. The stroke knowledge questions that will be asked are:

i.What type of stroke did you have?ii.What treatment have you had for your stroke?iii.Where in your brain did the stroke happen?iv.How has your stroke affected you?v.How can you reduce your risk of another stroke?vi.What new medication are you on?vii.What are the medications for?viii.What should you do if you experience symptoms of another stroke?

3. To complete the cognitive screening assessment, the Montreal Cognitive Assessment
^
46,
47
^ (MoCA) will be conducted in person where possible otherwise over the telephone or video call (T-MOCA
^
48
^) (T0 and T12).

4. To determine the feasibility of gathering self-reported health and social care usage data (attendance at GP and A&E for stroke-related concerns and new packages of care).

5. To complete qualitative interviews (T5).

6. To determine treatment costs based on appointment, administration and travel time.

7. To note which mode of follow-up is most preferred by participants and whether outcome measures can be effectively completed over the telephone.

8. To obtain feedback on the training manual and intervention delivery checklist from therapy and nursing staff.

### Qualitative data analysis

Participants in the control and intervention groups will be invited to participate in qualitative, semi-structured interviews. The focus of this will be to explore and understand the experience of receiving a diagnosis of stroke and life after stroke for those who received the intervention and those who did not. We will also seek to understand whether the intervention delivered was acceptable and how it could be improved. We will aim to conduct interviews with 15 to 20 participants.

Purposive sampling will be used to ensure that the views of participants from both groups and with a variety of demographic characteristics and experiences after their stroke are obtained. The interviews will be recorded and transcribed verbatim. The interviews will be face-to-face, either on video calls, in the clinic, or at the person’s home. A topic guide will be used, and the interviewer will maintain a field diary to capture reflections and thoughts.

We will review the quantitative measures alongside subjective reports from the participants to evaluate whether there is alignment of the qualitative perspectives and quantitative results. The planned purposive sampling strategy will enable the researcher to interview those who seemed to cope well with the transition back to their lives as well as those that appear to be having more adjustment difficulties. This will capture a diversity of experiences and perspectives.

We will explore whether the themes that arise from the qualitative data are captured in the quantitative measures used. Key concepts and themes that are prominent in the qualitative data will help the researcher to understand what matters to the participants. This also creates an opportunity for participants to introduce topics that may not be reflected in the outcome measures used in the feasibility study. Through these processes we aim to increase the likelihood of identifying a primary outcome for a subsequent definitive trial that is sufficiently nuanced to capture efficacy in a socio-culturally diverse population.

Alongside the study participants, family members that have supported the participant in the research study will be invited to participate in a separate interview. We will aim to conduct at least five interviews with family members.

The data analysis approach will be thematic using the six phases described by Braun and Clarke
^
49
^. This involves familiarising oneself with the interview transcripts to obtain initial ideas and thoughts and then producing initial codes from the data. Following this, the researcher looks more broadly at the codes to find themes in the data, comparing and contrasting findings across interview transcripts to consider any commonalities, differences, patterns, expected, and unexpected themes. These will be reviewed, using all supporting data to check for credibility and coherence, before refining the final themes and confirming how they interact and relate to each other prior to writing up the findings
^
49
^. Data will be analysed inductively, but emerging themes will also be considered in relation to Self-Determination Theory to assess the coherence of findings with the theory underpinning the intervention. Computer-assisted qualitative data analysis software (NVivo 14) will be used to support the analysis. Techniques to ensure rigour, such as reflexivity, will be used and reported to understand the researcher’s contextual, personal, and interpersonal influences on the research process
^
50
^. Peer reviewing of data with a clinical and academic colleague will be conducted, and where perspectives expressed are not clear during data analysis, these will be checked with the participants. Observations and comments noted during the follow-up appointments and the final outcome measure appointment will be referred to during data analysis to add further contextual information to the analysis. 

### Data management

All participants will be assigned a participant ID at the point of consent. Personal data and linking codes will be stored in separate locations using encrypted digital files and password-protected folders. The Case Report Forms (CRF) and questionnaires will only contain participant ID. Paper consent forms, pseudonymised CRFs, and questionnaires will be stored in secure NHS offices in locked cabinets. Scanned copies of the paper consent forms and questionnaires will be stored on secure NHS servers. All data will be collected in accordance with the Data Protection Act 2018 and in line with general data protection regulations (GDPR). Consent will be sought and in place for monitors and auditors from regulatory authorities to have access to identifiable information where relevant. 

Encrypted NHS devices will be used to record the interviews. Transcription of qualitative interviews will involve the transfer of voice recordings to a transcription service that has a data-sharing agreement with the sponsor. The participant ID will be used to label the audio files.

All study documentation will be archived in accordance with the sponsor policy. Data will be destroyed after 5 years.

### Statistical methods

The data obtained will be reported descriptively, and analysis will be conducted using Statistical Package for Social Sciences (SPSS) version 29. The primary analysis will focus on the feasibility outcomes and be presented as proportions with confidence intervals. The monthly recruitment rates will also be noted. Retention data will be noted by group (control and intervention) as well as overall and presented as proportions.

Baseline demographics and clinically relevant data will be reported to enable the understanding of participant characteristics and to enable other services to draw comparisons with their patient demographics.

The responsiveness of the outcome measures to change will be reviewed using confidence intervals for changes from baseline in each group and for between-group comparisons of changes. The numerical results and perceived relevance of the outcome measures used in this feasibility study will be considered. It should be noted that for the current feasibility study the outcome assessor is not blinded, and this has the potential to introduce bias in the assessment. The plan for a future definitive trial would involve a blinded outcome assessor.

The quantitative results will be considered alongside the qualitative findings to illuminate any individual or contextual insights from interviews that help to explain quantitative data. All of these will inform the choice of the primary outcome for a subsequent definitive trial evaluating efficacy.

The economic evaluation and feasibility of self-reported healthcare use will be explored. We will consider the treatment, administration, and clinician travel time to estimate the cost of delivering the intervention. Healthcare usage (GP and A&E attendance for stroke-related concerns) will be obtained from both groups. Self-report data will also capture those that are back at work in their previous capacity, as well as those that have not returned to work or are working in a part-time capacity. We will also capture data where packages of care have been started to support someone at home following their stroke.

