### Randomisation

Participants will be randomised to the intervention or control group by simple randomisation using a 1:1 allocation ratio and opaque sealed envelopes to ensure allocation concealment. Randomisation will be stratified by recruitment location to ensure treatment assignment is balanced between the two groups within each location.

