### Sample size

Progression criteria related to feasibility outcomes were identified. We plan to recruit 60 participants (30 in the control group and 30 in the intervention group) in line with sample sizes for similar feasibility studies
^
34
^. Feasibility studies need to be much smaller than full-efficacy trials to be considered worthwhile. The feasibility outcome “participant retention” is the percentage of 60 participants who complete outcome measurements at 12 weeks. Using a binomial probability confidence interval (CI) calculator with a sample size of 60, the 95% CI on proportions will have widths no greater than 37% (based on the 50% proportion having a 95% CI from 37% to 63%. Proportions further from 50% would have narrower CIs; for example, 90% has a 95% CI from 79–96%, so this CI has a width of 17%.
Free Binomial Probability Confidence Interval Calculator - Free Statistics Calculators (danielsoper.com)

The width of these CIs provides a reasonable balance between the cost and practicality of patient recruitment. The feasibility outcome “recruitment uptake” would have narrower CIs (since 60 is the numerator with a larger denominator). There is no relevant power calculation because the main outcomes are proportions rather than anything that can be assessed using hypothesis testing.

The progression criteria targets are described in
Table 4. They provide a guide through the use of a predefined traffic light system of red (stop), amber (amend, modifications needed), and green (proceed), as to whether the study could proceed to a future definitive trial. The targets may seem ambitious, but due to the limited number of appointments and personalised nature of the intervention, where participants do not need to attend appointments at the hospital, we believe these are achievable. We have carried out extensive work with diverse community groups that has improved our understanding of culturally appropriate ways to approach patients from different communities. Further, this is also a single-centre study, with the lead researcher having established working relationships with the other members of the stroke team.

**Table 4. T4:** Progression decision criteria.

FEASIBILITY OBJECTIVES	MEASURES USED	DENOMINATOR FOR PERCENTAGE	GREEN Proceed to full scale trial	AMBER Amendments needed	RED Definitive trial unlikely to be feasible
1. Recruitment uptake	% of eligible people agreeing to take part	Over 60 (numerator is 60)	≥90%	60–89%	<60%

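### For HCCQ, stroke knowledge and MoCA, a between-arm comparison adjusted for T0 score and location would usually be more precise than the planned comparison of raw changes

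*Protocol article*

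**What the plan says.** The Statistical methods section of the protocol article states that responsiveness of the outcome measures will be reviewed "using confidence intervals for changes from baseline in each group and for between-group comparisons of changes". The part at issue is "between-group comparisons of changes". The same section calls the whole analysis descriptive. It adds that the numerical results, together with perceived relevance and the qualitative findings, will inform the primary outcome of a definitive trial.

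The Randomisation section says "Randomisation will be stratified by recruitment location to ensure treatment assignment is balanced between the two groups within each location". The Sample size section gives 30 participants per arm and explains that "There is no relevant power calculation because the main outcomes are proportions".

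Table 5 and the Secondary feasibility outcomes section give these time points:

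- **T0 and 12 weeks:** HCCQ, stroke knowledge and the cognitive screen (MoCA, or its telephone version).
- **T1 (two weeks) and 12 weeks:** PROMIS10. Its first completion is described as part of the first intervention appointment.
- **12 weeks only:** PHQ9, GAD7 and PEI.

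**The concern.** The document itself names the change score as the quantity to be compared between arms, so this is a stated choice and not a detail left open. Subtracting the baseline forces its coefficient to be 1. When the true slope of the 12-week score on the T0 score is below 1, this adds noise. It also over-corrects for any chance difference between arms at T0: the arm that starts lower tends to show the larger gain through regression to the mean.

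At stake is the between-arm evidence on which measure to carry forward. Wider or imbalance-driven intervals make that evidence less informative. The definitive trial will also need a residual SD and a baseline correlation, and a comparison of changes does not report them directly.

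A second problem sits in the same sentence. A change from baseline cannot be formed for PHQ9, GAD7 or PEI, and for PROMIS10 it cannot be formed from a value taken before randomisation.

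**Working it through.** **Plan's own figure.** The document gives no precision figure for this comparison. Its only precision figures are exact binomial intervals for the feasibility proportions. Those limits reproduce (30/60: 36.8% to 63.2%; 54/60: 79.5% to 96.2%) but have no bearing here.

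**Inputs.** From the Sample size section: N = 60, n = 30 per arm. Assumed, because the document gives no value: SD = 1 at both times, correlation r from 0.3 to 0.95, and a 95% level for these intervals.

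**Formulas (half-width of the 95% interval, in SD units).**

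- Change score: t(N−2) × √[2(1−r)] × √(2/n).
- Adjusted for T0 score and location: t(N−4) × √(1−r²) × √[(2/n)(1 + 2/(N−5))]. The last factor and the smaller degrees of freedom charge for the two covariates. Location is given no prognostic value.

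**Worked case, r = 0.5.** Change: 2.002 × 1.000 × 0.258 = 0.517. Adjusted: 2.003 × 0.866 × √(0.0667 × 1.0364) = 2.003 × 0.866 × 0.263 = 0.456. The ratio is 0.882, so the adjusted interval is 12% narrower.

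| r (assumed) | Change | Adjusted | Ratio, N = 60 | Ratio, N = 36 |
|---|---|---|---|---|
| 0.3 | 0.612 | 0.502 | 0.821 | 0.834 |
| 0.5 | 0.517 | 0.456 | 0.882 | 0.896 |
| 0.7 | 0.400 | 0.376 | 0.939 | 0.953 |
| 0.9 | 0.231 | 0.230 | 0.993 | 1.008 |
| 0.95 | 0.163 | 0.164 | 1.006 | 1.021 |

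N = 36 is 60% retention, the lower edge of the amber band in Table 4. At 90% retention (N = 54) the ratios are within 0.002 of those at N = 60.

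**Simulation check.** 3000 datasets were run for each r, with simple 1:1 allocation. The assumed split was 43 from the HASU and 17 from the RAC, following the monthly targets of five and two (60 × 5/7 ≈ 43). Mean width ratios were 0.824, 0.882, 0.939, 0.994 and 1.005 for r = 0.3, 0.5, 0.7, 0.9 and 0.95. The adjusted interval was the narrower one in 99.6%, 98%, 88%, 51% and 36% of datasets. Coverage was 94% to 96% for both methods at every r, so the planned interval is valid.

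**Chance imbalance.** The standard error of the T0 difference between arms is √(2/30) = 0.258 SD. A T0 difference d shifts the expected change-score difference by −(1−r)d. At r = 0.5, a one-standard-error imbalance therefore moves it by 0.5 × 0.258 = 0.13 SD. The adjusted estimate removes this shift.

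**Low correlation.** At r = 0.3 the change score has variance 2(1−0.3) = 1.4, against 1.0 for the 12-week score alone. For any r below 0.5, subtracting the baseline is worse than not using it.

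**The case against.** The strongest case against is that nothing here is wrong. The article says "The data obtained will be reported descriptively, and analysis will be conducted using Statistical Package for Social Sciences (SPSS) version 29". There is no hypothesis test, coverage is nominal, and the progression criteria in Table 4 use only recruitment, adherence and retention. The choice of a future primary outcome has no interval-width threshold, and no case is shown in which an interval 6% to 18% narrower would change it. All of that stands, and it limits the weight of the point.

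Several stronger readings are tempting but not supported:

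- **That the plan ignores the stratification factor.** The article neither names nor excludes covariates. They may be set out in the full protocol or an analysis plan that is not shown. Location is in the proposed model because the Randomisation section stratifies by it, not because its omission is established. It adds precision only if it predicts outcome.
- **That adjustment is always narrower and free.** At this sample size the gain is gone near r = 0.9 and slightly reversed at 0.95. Even at r = 0.7 the adjusted interval was not narrower in about 12% of simulated datasets.
- **That within-arm change is misused.** The text speaks of how measures respond to change, not to this intervention. Movement of a scale from the first week after stroke to 12 weeks is a fair description of that property, even though it mixes recovery, retesting and care. It would mislead only if read as an intervention effect.
- **That one adjusted model can serve every measure.** Of the five patient-reported measures listed to inform the main trial's primary outcome, only HCCQ has a T0 value. Using the T1 PROMIS10 score as a covariate would adjust for something measured after randomisation, which the intervention may already have affected.

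MoCA carries one further caution. It may be taken in person or remotely, so its two readings may not be on the same version.

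**Conclusion.** The point holds as a modest efficiency improvement. For HCCQ, stroke knowledge and MoCA, the planned comparison of raw changes is valid but usually less precise than one adjusted for T0 score and location. It is also exposed to chance baseline imbalance at about 30 per arm. The gain at N = 60 is about 18%, 12% and 6% in interval width for r = 0.3, 0.5 and 0.7, and essentially nothing near 0.9. These figures rest on assumed correlations and equal SDs at the two times; the document supplies neither. Separately, and without any assumption, the sentence on changes from baseline cannot be carried out for PHQ9, GAD7 and PEI, nor from a pre-randomisation value for PROMIS10. A reader might infer that the planned intervals are invalid or that the go/no-go decision is affected; neither follows from the document.

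**What to change.** In Statistical methods, replace the between-group part of the responsiveness sentence with text to this effect:

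> For measures with T0 and T4 values (HCCQ, stroke knowledge, MoCA), the between-arm difference at T4 will be reported with a 95% CI from a linear model with arm, T0 score and recruitment location, together with the residual SD and the baseline-to-T4 correlation. For PROMIS10, PHQ9, GAD7 and PEI, arms will be compared at T4 adjusted for recruitment location; the T1 PROMIS10 score will not be used as a baseline covariate. Within-arm changes will be reported as a description of how each scale moves, not as evidence of an intervention effect.

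The cost is two degrees of freedom and one extra general linear model per measure, which the named software handles routinely. No new data are needed. The Trial status section says outcome measurement is still under way, so by that account the change can be made before the analysis.

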### Data monitoring

The study is sponsored by Imperial College Healthcare NHS Trust (ICHNT) and has been reviewed and received approval by the Imperial College London and ICHNT Joint Research Office. The principal investigator will ensure day-to-day management of the trial and will be overseen by the Chief Investigator. The study management group will have an independent chair and two lay members. It will monitor the progress of the trial, recruitment rate, adherence to the protocol, and completion of outcome measures to ensure that the study is progressing as planned. An independent data-monitoring committee is not indicated.

